## Abstract

**Background:** Infancy is an important period in a child's life, with rapid growth and development. Early experiences shape the developing brain, and adverse experiences can have both an immediate and lifelong impact on health and wellbeing. Parenting interventions offered to parents of newborns can support parents in providing sensitive and responsive care, and reinforce healthy development for their infants. This study aims to evaluate the impact of the Incredible Years™ Parents and Babies Program in a universal setting for parents with infants.

**Methods/Design:** This is a pragmatic, two-arm, parallel, pilot, randomized controlled trial (RCT) where 128 families with newborn infants up to four-months-old are recruited in two municipalities in Denmark. Families are randomized to the Incredible Years Parents and Babies Program or usual care with a 2:1 allocation ratio. The primary outcome is parenting confidence measured after 20 weeks by the Karitane Parenting Confidence Scale and Parental Stress Scale. Secondary outcomes include measures of parent health, reflective functioning, relationship with the infant, and infant development. Interviewers and data analysts are blind to allocation status.

**Discussion:** This is the first RCT of the Incredible Years Parents and Babies Program, and one of the first rigorous evaluations of a universally offered preventive intervention for parents with infants. The trial will provide important information on the effectiveness of a relatively brief, universally offered parenting intervention for parents of infants, and will also provide information on infant measures, parent recruitment and participation, and implementation of the program, which could inform future trials.

**Trial registration:** This trial was registered with Clinicaltrials.gov (identifier: NCT01931917) on 27 August 2013.

**Keywords:** Parenting, Parenting interventions, Early intervention, Early childhood, Infants, Incredible Years™, Randomized controlled trial, Universal intervention, Prevention

Correspondence: [contact]

SFI - The Danish National Centre for Social Research, Department for Children and Family, [name]

University of Copenhagen, Department of Public Health, [name]

## Background

Substantial evidence has documented the importance of a child's experiences in the first years of life, linking adverse experiences in childhood to later conditions in life, such as depression, health problems, drug abuse, teen pregnancy, and delinquency [1–4]. The relationship is cumulative, as greater numbers of stressful life events in early life results in a greater risk of negative outcomes later in life [2, 5]. The quality of the attachment relationship between the infant and their parents is pivotal in the early years and greatly influences the child's social, emotional, and cognitive development [6]. A secure attachment to the caregiver predicts a healthy development, whereas an insecure attachment is related to later behavior problems and poor peer relations [7]. It is therefore crucial that appropriate parenting interventions are available to families with infants, especially since interventions in early childhood have been shown not only to be effective [8–13], but also to be more effective than interventions later in life, because it is easier to intervene before problems become entrenched [1, 14].

Parent interventions can be either targeted or universal. In a targeted intervention, families are singled out and offered the intervention because they are thought to be at risk and/or in need of help [15]. Universal interventions on the other hand, are directed at all residents in a specific geographic area and no one is singled out for intervention [15]. Universal interventions have both advantages and disadvantages. The main advantages are: that there is no labelling or stigmatization involved, that the quality of the interventions tend to be high because the middle class is involved, and that at-risk families can be identified and offered more help if needed [15, 16]. The main disadvantages are: that universal programs are expensive, the individual benefits tend to be small, and it can be difficult to find overall effects. Further, it might enlarge social inequality if well-functioning families benefit the most from the interventions [15, 16]. A targeted approach is often applied, but relies on correct identification of families in need of support, which is challenging, as screening instruments never are perfectly accurate, and many families with risk factors do well whereas families with no risk factors might experience difficulties [16]. Child behavior problems tend to be normally distributed across the population, and many families experiencing problems would be missed by a targeted approach based on risk factors [17]. A universal population-level approach is therefore needed to be able to best prevent child developmental problems [17–19].

There are, however, only a few trials of parenting interventions adopting a universal approach [20–27]. Only one of these trials is in a group format and is delivered only postpartum: the Toddlers Without Tears program that was recently evaluated in a randomized controlled

trial (RCT) in Australia [25, 28]. Even though the trial was powered to detect a small effect size, only modest improvements in parenting risks were found, but no impact on child behavior at follow-up time points of 18, 24, or 36 months was found. The authors concluded that, 'A brief universal parenting programme in primary care is insufficient to prevent development of preschool externalising problems' [25]. Compared to the Toddlers Without Tears program, the Incredible Years™ Parenting and Babies Program (IYPB) offers significantly more sessions (eight compared to three), and starts when the infant is younger (preferably between zero and four months compared to eight months). In this pilot trial, a more intensive intervention offered as a universal approach aimed at a community sample of parents with newborns is evaluated.

An important challenge when performing trials with infants is deciding on primary and secondary outcome measures. Often measures yielding important information on how the parent changes over time, such as measures of parent depression, parenting stress, parenting competence or confidence, or parenting practice are used. Observational measures such as the Bayley Scales of Infant and Toddler Development, the Mullen Scales of Early Learning, and the Strange Situation procedure are also frequently used in infant studies. However, despite it being one of the primary areas targeted by parenting interventions, it is not as common to assess infant development, in particular social-emotional development, using parent-report measures. Infant development is arguably the most difficult construct to measure, as it occurs rapidly, dramatically changes within the first years of life, and it is widely influenced by family and culture values [2, 29–31].

Within recent years a few protocols for infant trials have been published [32–37], but none of these are aimed at universal or low risk populations. Given the relatively low numbers of infant program efficacy or effectiveness trials conducted in this emerging field, it is useful for researchers to learn about some of the possible measures that can be used. In addition, it has been common in the published research in the field to only report on measures where there are significant findings, so researchers designing studies do not know which measures to consider or leave out. In the present trial, a wide array of both parent and infant development measures are used, hopefully aiding future researchers to identify appropriate primary and secondary outcomes for trials on infants.

Parent-infant relationships and parenting practices are central to early-onset social-emotional or problem behaviors, such as aggression or disruptive behaviors [3]. Parenting interventions therefore aim to target these two areas and to support parents in providing sensitive

and responsive care to their children. Incredible Years (IY) is a parenting intervention with a focus on strengthening parenting competencies and promoting children's social, emotional, and academic competence. IY was developed by Carolyn Webster-Stratton more than 30 years ago, and offers a range of programs for parents and teachers of children aged from 0 to 12-years-old. The IY programs are used as both universal and targeted interventions in more than 24 countries worldwide.

IY programs have been evaluated in several RCTs and meta-analysis and were found to be effective on both parent and child outcomes [3, 9, 38–45]. A recent meta-analysis of IY interventions for children between three and nine-years-old shows a mean effect size of  $d = 0.27$  for disruptive behavior across informants [38]. Outcomes that were based on parent reporting showed larger effect sizes for targeted approaches (treatment studies  $d = 0.50$ ) than universal approaches (indicated sample  $d = 0.20$ , selective  $d = 0.13$ ). There were larger effects for children with severe problems. Another recent meta-analysis based mainly on IY studies [9] of children between three and 12-years-old shows standardized mean differences (SMD) of  $-0.53$  for parent reports and  $-0.44$  for independent reports on child conduct problems. Negative or harsh parenting practices were also reduced (SMD:  $-0.77$ ) and the intervention was cost effective. The only published study on the effects of IY on children younger than three-years-old is an RCT from Wales of the IY Parent-Toddler program that looked at the effects on parental language [46]. The trial indicated positive effects on two out of five language outcomes. Therefore, although there are very positive results of the IY intervention on both parenting and child outcomes for children three-years-old and older, there is very little knowledge on the effects of IY on children younger than three-years-old.

## Methods/Design

The trial is a pragmatic, two-arm, parallel, pilot RCT carried out in two municipalities in Denmark. Figure 1 shows the design of the trial. The trial is an external pilot study in the sense that it is a separate trial.

## Eligibility criteria

Eligible participants are mothers with infants living in Ikast-Brande or Herning municipalities in Denmark. Ikast-Brande (population 40,620) and Herning (population 47,765) are bordering municipalities located in central Jutland. If a father is present, he is also invited to participate in the trial.

All mothers in Denmark are entitled to 46 weeks of maternity leave after the birth of a child. The first 14 weeks are exclusively entitled to the mother, but the remaining 32 weeks can be shared with the father. Fathers are entitled to two weeks of parental leave after the birth. This means that almost all mothers participating in the study will be on maternity leave with the child when the intervention is being offered, and will remain on maternity leave until the child is somewhere between six and 12 months. At 12 months, around 81 % of children in Denmark attend daycare [48], so most children will be in daycare at the time of the 18-month follow-up assessment. All municipalities offer free home visits by health visitors to families with newborns and children up to the age of six-years-old. Virtually all families (between 97 and 99 %) take up the offer. Most families receive five to six visits within the first year, but the number is suited to the needs of the family. Families are also offered three child health visits at the general practitioner within the first year after birth [49, 50].

## Inclusion criteria

Mothers with infants aged up to four months who are able to read and write Danish may be included in the trial. In Ikast-Brande, only primiparous (that is, have

[figure not shown]

given birth for the first time) mothers are invited; in Herning primi- and multi-parous mothers living in certain districts of the city are invited.

### Exclusion criteria

Families are excluded if they do not fulfill the inclusion criteria or if they fulfill one or more of the following exclusion criteria: a severe physical or mental disability in parent or child (for example, parents with severe schizophrenia, severe substance abuse, or a child with congenital disease like cerebral palsy) or if the child is placed in out-of-home care.

### Intervention care and comparison

#### Intervention

The families randomized to the intervention group receive the IYPB. The IY programs are based on Bandura's modeling and self-efficacy theories, Patterson's social learning model, and Bowlby's attachment theory. The main foci of the intervention are promoting a warm and nurturing parent-child relationship, enhancing parenting competencies, and encouraging a parent involvement to promote children's social, emotional, and academic skills and reduce conduct problems [51].

Parents learn through the IYPB how to help their babies feel safe, loved, and secure, and how to promote their babies' physical, emotional, and language development. The parenting group format stimulates shared learning and peer support networks. Parents practice new skills with babies within the group and are encouraged to try out ideas at home as part of weekly home

assignments. Parents also share updates on their infants' development and activities in a safe and supportive environment [51].

The IYPB uses video vignettes of real-life situations with parents and babies to support the training and to foster discussion in the group. The original American video vignettes are used, with Danish subtitles added. Group leaders also use a Baby Brain Poster with a picture of the brain of a crawling baby to explain to the parents the importance of the development of the infant brain, and how they can strengthen neuron connections and help the brain development of their infant. Parents are furthermore provided with the book *The Incredible Babies* [52], which has been translated into Danish [53]. The book describes how to promote child development and includes a journal section. Before the book was translated, parents were provided with refrigerator notes that included relevant information on, for example, child development or activities the parents could do with their infant to promote child development.

A group is made up of six to eight parents and is led by two trained group leaders. Mothers bring their babies to the sessions, and partners are strongly encouraged to participate. If the mother is single, she can bring a family member such as her mother or sister, if she wants. The program consists of eight sessions of two hours. The parents can arrive half an hour before and eat lunch if they wish. The sessions run every week or every two weeks. The six parts that are covered during the course are: Getting to Know Your

Baby; Babies as Intelligent Learners; Providing Physical, Tactile and Visual Stimulation; Parents Learning to Read Babies' Minds; Gaining Support; and Babies' Emerging Sense of Self. The group leaders follow a manual to ensure that the intervention is delivered with fidelity [51].

### **Control**

The families randomized to the control group receive usual care (UC). UC consists of four to five home visits by health visitors, open consultation hours at a local well-child clinic, voluntary participation in a group of six local mothers, and extra support if needed (for example, extra home visits, family therapy, or video feedback intervention). The intervention group is offered the IYPB on top of UC. UC is consistent with what is offered in the majority of Danish municipalities. The control group families cannot get access to the IYPB, but both they and the intervention group might participate in other infant activities offered by private organizations, such as hymn song at the local church or baby massage classes.

### **Procedure**

The trial is registered by The National Committee for Health Research Ethics (reference number H-2-2013-FSP60, and has received ethical approval from the Internal Research Council at SFI - the Danish National Center for Social Research. The trial is registered at Clinicaltrials.gov (reference number NCT01931917).

Recruitment is performed by health visitor, social workers, or midwives in the municipalities. Families are provided with oral information, an information sheet, a two-minute YouTube video (available at [www.sfi.dk/godtrivsel](http://www.sfi.dk/godtrivsel)) with information on the trial, and a consent form. After receiving the initial consent from the family, the contact person in the municipality sends the contact information to the trial coordinator. An interviewer contacts the mother and sets up an interview in the home. At the T1 visit, written informed consent to participate in the trial is obtained from each mother (and father if he wishes to participate in the trial) and T1 measures are collected. All participants are informed that they can withdraw from the study at any time without their rights being affected.

### **Randomization**

An independent researcher computes a random allocation list stratified by municipality and with a block size of three. The allocation ratio is 2:1 (IYPB:UC), as it is important for the municipalities to have enough families in the IYPB intervention arm to start the groups. After the baseline assessment is completed, the interviewer informs a designated research

administrator that the interview has been completed. The research administrator then randomizes the family by adding the name to the randomization list in the order the names arrive from the interviewer. Then the contact person in the municipality is informed about the allocation status of the family. Participants are informed by their health visitor as to which arm of the study they have been allocated to. In the case where consent to treatment is withdrawn but the participant agrees to remain in the research study, the participant is followed to completion.

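### A fixed block of three at 2:1 within municipality, with allocations fed back to those who recruit and refer, makes up to 44% of allocations certain in advance

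*Protocol*

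**What the plan says.** **List.** Protocol, Randomization: the allocation list is drawn up by an independent researcher, "stratified by municipality and with a block size of three". The ratio is 2:1 in favour of IYPB, and the Methods/Design section says the trial is "carried out in two municipalities in Denmark", so there are two strata. No variation in block size is mentioned, and nothing is said about keeping the block size from municipal staff.

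**Who recruits and refers.** Protocol, Procedure: "Recruitment is performed by health visitor, social workers, or midwives in the municipalities". After initial consent, "the contact person in the municipality sends the contact information to the trial coordinator".

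**When and how families are allocated.** Randomization follows the T1 visit, at which written consent is taken. A research administrator does it by "adding the name to the randomization list in the order the names arrive from the interviewer".

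**Who learns the result.** The municipal contact person is told each family's arm, and "Participants are informed by their health visitor as to which arm of the study they have been allocated to". The Blinding section adds that health visitors, like group leaders, will know which families are in the intervention arm. Interviewers are blind.

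**Baseline measures.** Table 1 and the Primary outcomes section show the KPCS at T1 and T2, and the PSS at T2 and T3 only. The Planned statistical analysis section adjusts for the baseline score where one exists.

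**The concern.** Three is the smallest block that a 2:1 ratio allows, and therefore the most predictable. Once the usual-care place in a block has been used, what remains is certainly IYPB. If the first two places are IYPB, the third is certainly usual care.

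Predictability does harm only if it reaches someone who can influence who enters next. Here it can. The contact person handles both the outgoing referrals and the incoming allocations for the municipality, and health visitors both recruit and know allocations. A recruiter worried about a mother might hold her back when a usual-care place is due, since controls cannot get the programme. A municipality short of families for a group might bring others forward.

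Randomizing after consent and T1 keeps a known allocation from affecting T1 data. It does not protect the earlier decision about whom to approach or forward, or when. The planned separate analyses of parents with poor baseline scores concern the very families most likely to be steered.

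**Working it through.** The protocol gives no predictability figure, so there is none to reproduce.

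**Inputs.** Block size 3, ratio 2:1 and stratification by municipality (Randomization); 128 mothers (Sample size). Write I for IYPB and C for usual care. Each block is IIC, ICI or CII, each with probability 1/3.

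**Certain allocations, full information.** Count an allocation as certain if the earlier ones in its block leave only one possible arm.
- Position 1: never certain, 0.
- Position 2: certain only if position 1 was C, 1/3.
- Position 3: always certain, 1.
- Expected share: (0 + 1/3 + 1)/3 = 4/9 = 44.4%, or 128 × 4/9 ≈ 57 families.

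**Best guess, full information.**
- Position 1: guess I, right with probability 2/3.
- Position 2: after C (probability 1/3) the guess is certain; after I (probability 2/3) it is right half the time. Together 1/3 + 2/3 × 1/2 = 2/3.
- Position 3: always right, 1.
- Mean: (2/3 + 2/3 + 1)/3 = 7/9 = 77.8%, against 66.7% for always guessing IYPB.

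**If information lags.** Suppose the block boundaries are known but the latest allocation in the municipality is not.
- Position 3 is then certain only if position 1 was C (1/3), and positions 1 and 2 are never certain.
- The share is (0 + 0 + 1/3)/3 = 1/9 = 11.1%, or 128 × 1/9 ≈ 14 families.
- If the last two allocations are unknown, nothing is certain and the share is 0.

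**How likely is a lag?** The protocol does not give the interval from referral to allocation. Trial status puts recruitment from August 2013 to the end of summer 2015, about 24 months. Assuming an equal split and steady accrual, each municipality enrols 64 families in about 730 days, or one every 730/64 ≈ 11 days. At that pace feedback before the next referral is plausible, but the text does not establish it.

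**Alternatives, full information on earlier allocations.** The first three rows are exact enumerations. The last is a simulation assuming 64 families per municipality and a guesser who knows the set of sizes but not the sizes drawn.

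| Block scheme | Certain share |
|---|---|
| Fixed 3 | 4/9 = 44.4% |
| Fixed 6 | 13/45 = 28.9% |
| Fixed 9 | 3/14 = 21.4% |
| Random 3 or 6, undisclosed | about 10% |

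A larger fixed block helps only in part. Most of the gain comes from varying the size and not disclosing it.

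**Longest possible run of controls.** With blocks of three it is 2 (IIC then CII). With blocks of six it is 4 (IIIICC then CCIIII).

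**The case against.** The strongest reply is that 44% describes an ideal observer whom the protocol never places in the trial. That observer must know the block size, where each block starts and every earlier allocation in the municipality. The route from recruiter to contact person, coordinator, interviewer and home visit adds delay. List position follows the interviewer's reports, not the order of referral. Only the contact person is said to be told family by family. A health visitor passing on the arm to her own families need not see the whole sequence, and nothing says that social workers or midwives learn allocations. All of this stands, and it is why the figure must be read as a ceiling with a range down to zero.

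It does not remove the point. The contact person sits on both sides of the process, the protocol does not say that the block size is withheld, and a pattern of one control in every three is easy to notice.

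Three stronger readings are tempting, and the protocol does not support them:
- **That the administrator can see upcoming arms.** The Randomization section says names are entered on a list in order of arrival. It does not say whether later entries are visible, and it gives the administrator no part in recruitment. Concealment is not stated; its absence is not shown.
- **That no analysis could help.** T1 precedes allocation, so adjusting for T1 KPCS deals with imbalance in that measured score. It does not deal with unmeasured differences, and no such adjustment is available for the PSS.
- **That self-report by unblinded parents makes this worse.** That is a separate source of bias and adds nothing to the argument about selection.

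**Conclusion.** The point holds as an avoidable risk of selection bias at the approach or referral stage. Between 0 and 44% of allocations could be certain in advance. The upper end needs knowledge of block size, boundaries and all earlier allocations in the municipality; 11% applies if the latest allocation is missing, and 0 if the last two are. The protocol does not allow a narrower range.

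A reader might infer that 44% of allocations were in fact foreseen, or that families were steered. Nothing in the protocol shows either. The KPCS comparison is partly protected by T1 adjustment. The PSS comparison, also primary, lacks that protection.

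**What to change.** For any allocations still to be made, and in the future definitive trial:
- Have the independent researcher generate permuted 2:1 blocks of randomly varying size, for example 3 and 6, within municipality.
- Withhold the block sizes from municipal staff and interviewers.
- State in the protocol that each upcoming assignment is concealed until completion of T1 has been logged.

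The protocol does not show how many allocations remain. If recruitment is nearly complete, the benefit lies mainly in the definitive trial.

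**Cost.** One new list from a researcher already involved, and a possible small departure from 2:1 at the end of a stratum. Longer runs of controls also become possible, up to 4 against 2 now. Since 2:1 was chosen so that municipalities could fill their groups, and a group has six to eight parents, such a run could slightly delay a group's start. Keeping the largest block at six limits this.
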